## Ethics and dissemination

The study will be carried out according to the Good Clinical Practice guidelines of the Declaration of Helsinki.^38^ Informed consent is obtained from each patient to take part in the study and for their clinical records to be reviewed. This project was approved by the corresponding ethics review board of the Malaga Provincial Research Ethics Committee on 25 February 2021.

The database is hosted on the secure REDCap platform at the University of Málaga, Spain. REDCap is an important tool for data access, linkages and mobilisation. On agreeing to participate in the project, clinics receive a random identification code, and the principal investigator and statistics team is blind to the coding.

All results and conclusions drawn from this project will be disseminated through local presentations, national or international meetings, academic publications and feedback to project participants.

In addition, as this project is funded by the La Caixa Foundation, the main results of the study will also be published for dissemination to the general public in different articles uploaded on its website.

## Discussion

The COVID-19 pandemic is changing the way we are interacting, launching us seemingly overnight from the real world into the virtual world, and seeking ways to address the challenges of social distance.^39^ Face-to-face support of PC volunteers has temporarily been suspended, so creativity and innovative solutions are needed to continue providing this care and support. The use of information and communication technologies and, specifically, NT, allows us to rethink the way volunteers act by integrating these resources to create ‘tech-volunteers’ that will attend to their needs in a different way and also support new needs that have emerged more clearly now due to social distance, with a broader reach.^40^ The United Nations Online Volunteer Programme states: ‘Online volunteering is fast, easy—and most of all, effective when skilled, passionate individuals join forces online with great organisations, everyone wins’ but no robust study has been carried out to support this statement. In this way, this study will bring the real evidence toward NT integration as a useful tool not only to facilitate communication between volunteers and patients/relatives, but also to turn NT into instruments that support daily living and enhance care, when in the hands of trained tech-volunteers.

Although this new volunteer programme will be implemented during the pandemic to analyse the effects on patients and their relatives, we hope that training in NT will make it easier for PC volunteers to offer new skills and increase the satisfaction of the people they accompany.

The implementation of this study has some limitations that we will try to control for and take into account. For example, in pragmatic cluster randomised controlled trials, the first bias to take into account is the selection bias, as the randomisation is usually applied in the second level, before recruitment of the first-level participants, which is where the intervention impact is measured. However, there are strategies that minimise this bias. First, the selection and follow-up of patients will be carried out by an external researcher who will have no knowledge of volunteer randomisation. Second, the effect of the intervention over recruitment can lead to different recruitment indexes, depending on the groups, due to the possibility that volunteers will be allocated a group in which they do not feel comfortable (eg, a volunteer who does not like the NT—technophobe—and will be allocated the intervention group) could be less motivated to participate. This issue will be taken into account in the analysis and it will be a result of the implementation process. There could be measurement bias due to mistakes in recording of some variables or interviewer bias due to the administration of the questionnaires. To minimise these biases, interviewers will have been trained previously to ensure that visits will be as homogeneous as possible. A data collection booklet and a manual that explains how each variable is measured will be designed.

Another bias that has already been mentioned is the involvement of volunteers in the year they will collaborate in ITV-Pal. For this reason, more volunteers will be trained. But also the number of patients/volunteers needed to achieve a representative sample and draw conclusions will be difficult to achieve in the 2 years of piloting the study.

Maybe the principal risk in this study will be that we will not be able to attend to the different needs of patients/relatives. In this case, we will try to adapt by offering other volunteers who may be able to give a better response to this need.

Due to the fact that in this study, we want to assess the implementation of an intervention programme, all these issues that we might find during the process could contribute to an improvement of the programme and would be useful for new research and the implementation of new interventions in the future.

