**Trial registration number:**

NCT04900103.

STRENGTHS AND LIMITATIONS OF THIS STUDYThe use of a mixed model that combines qualitative and quantitative methodology is the best way to evaluate the implementation of a new service, which is why it will be the one chosen in this study.One of the limitations of the study is the effect of the intervention on recruitment and that this may result in different recruitment rates.The main risk of this study is that we will not be able to attend to the different needs of the patients/families, although we will try to offer volunteers who can provide a better response to these needs.

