#### A: Quantitative approach

Pragmatic cluster randomised clinical trial to test efficacy (the unit of randomisation is the volunteer and the unit of analysis is the patient/relatives). A pragmatic cluster randomised controlled trial has shown to be the most appropriate design when the programmes are more focused on the organisational level.^22 23^ For our study, the cluster design is based on two levels: the higher or second level is represented by the volunteer (over volunteer the intervention is conducted, ITVPal Programme: Tech-Volunteer Programme in Palliative Care Services), and the lower or first level being represented by the patients/relatives, who have agreed to participate and are going to receive the tech-volunteer care from volunteers of ITVPal Programme.Before-and-after design for satisfaction of volunteers and HPC with the intervention and its implementation to test effectiveness. The design involves evaluating the effects of a deliberate intervention (introduction of ITVPal Programme) by comparing the outcomes of study participants investigated before the intervention with those measured afterwards.Cost–utility study from the perspective of the funder with a time horizon of 2 years. A detailed cost analysis including costs for the adaptation of a volunteer standard course to an ITVPal Programme as well as the recruitment and training costs of the volunteers will be performed.

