### Settings

The study will be conducted in a palliative care unit from both a home care and an inpatient unit of the CUDECA foundation.

The hospitalisation unit is a small hospice consisting of 10 rooms where patients at the end of life are cared for in cases of uncontrolled symptoms, for family respite or in their final days, among other situations. In this unit, volunteers come every afternoon to the rooms where they wish to offer accompaniment to patients and their relatives.

In addition, CUDECA foundation provides home care to more than 1500 patients a year through 7 care teams made up of a doctor, nurse, psychologist and social worker. In these cases, the volunteer accompanies patients and relatives who wish them to do so.

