### Randomisation

The radomisation will take place in the higher or second level represented by the volunteer (over volunteer the intervention is conducted: ITVPal Programme) using a block randomisation technique. Each block is formed by four volunteers among whom the two study arms will be uniformly distributed. Once the blocks have been created, they will be distributed using a sequence of random numbers and the final list of volunteers allocations will be created. The final list of volunteers allocations will be guarded by the principal investigator of the project, and he will inform the allocation of each volunteer included in the trial.

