#### Intervention

A complex intervention will be carried out in two phases.

First phase: training of volunteers in NT. Volunteers will be trained in the use of NT and their interconnectivity as tools to support their work as volunteers.The topics that will be covered in the volunteer training are the role of the volunteer, use of NT, communication strategies, complicated situations, self-care, summary and closure of the training. All of this is divided into 10 sessions, each lasting approximately 3 hours. This training will be integrated into the specific training programme for PC care volunteers.The control group, on the other hand, will receive the standard training that the care volunteers have received so far.Second phase: volunteer accompaniment of patients/relatives. During the activities carried out by the volunteer with the patient for accompaniment and leisure. It will have the support of a technological device to be used according to the needs of the patient/relatives (eg, internet searches on a topic of interest, video calls, phone calls, virtual visits) It will be an outcome of the study to know what the device has been used for.The control group will accompany patients without using the NT as usual.

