### Data collection and follow-up

The recruitment of the volunteers began in March 2021. When they finished their training, the new service started in September 2021 which was when patients/relatives recruitment started. Volunteer recruitment will be active during the whole study every 3 months. Recruitment is expected to end in September 2023.

The care teams offer the accompaniment of a volunteer to the patient/relatives. If they accept the accompaniment and participate in the study (if they want the accompaniment of a volunteer but do not want to participate in the study, the volunteer will be offered anyway). Once the informed consent to participate in the study has been signed, the data collection will proceed as described below. Further details can be seen in figure 1.

Patients/relatives who consent to participate (intervention and control group) will be invited to fill in at least three short questionnaires: at the time of recruitment for this study, 15 days after recruitment following the volunteer service experience (if hospitalised), and every month as long as the patient remains under PC care or until death. During the follow-up, patients and relatives will be asked if there is any change in their condition with respect to the questions asked at baseline. In this way, costly follow-up will be avoided. A maximum of 5 patients/relatives will also be invited to participate in an in-depth interview at various points during the implementation of the programme.

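### Patients may be offered a replacement volunteer by need with no limit to the same arm, and no arm-independent rule fixes which arm a patient is in

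*Protocol article*

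**What the plan says.** The article (A: Quantitative approach) sets up a cluster trial in which "the unit of randomisation is the volunteer and the unit of analysis is the patient/relatives". Under Randomisation, allocation concerns volunteers only: "Each block is formed by four volunteers among whom the two study arms will be uniformly distributed". Patients and relatives are recruited afterwards and take their arm from the volunteer they receive.

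The arms differ in what the volunteer brings. Under Intervention, trained volunteers carry a device to be used as the patient or relative needs it, for example for video calls or internet searches. For the other arm, "The control group will accompany patients without using the NT as usual".

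On how a patient comes to have a particular volunteer, Data collection and follow-up says only "The care teams offer the accompaniment of a volunteer to the patient/relatives". The one forward-looking statement about choosing a volunteer concerns unmet needs. The Discussion says "we will try to adapt by offering other volunteers who may be able to give a better response to this need", and the strengths and limitations list near the front gives the same answer to the same risk: "we will try to offer volunteers who can provide a better response to these needs". Neither place limits the alternative volunteer to the same arm.

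The Discussion recognises that randomising volunteers before recruiting patients invites selection bias. Its safeguard is that "the selection and follow-up of patients will be carried out by an external researcher who will have no knowledge of volunteer randomisation". Data analysis names intention to treat and a multilevel model with clustering by volunteer.

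**The concern.** Randomising volunteers makes the groups of volunteers comparable. It makes the groups of patients comparable only if the link from patient to volunteer, and any later change of that link, does not depend on patient characteristics that differ by arm. The article gives no such rule for the first link, and for later changes it names need as the criterion.

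Need is not neutral here. Whether a volunteer can answer a need for remote contact or online information depends on arm, because only one arm uses technology. Such a need may also go with isolation, distress and attitude to technology, and the trial measures social support, distress, anxiety and depression, and technophilia.

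Three things are at stake:

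- **Dilution.** A control participant who moves to a tech-volunteer receives the intervention.
- **Bias.** If a participant is counted under the volunteer they ended up with, the arms are partly sorted by need.
- **An undefined analysis.** Intention to treat and clustering by volunteer both assume one arm and one cluster per participant. The article does not say which applies to someone who had two volunteers.

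**Working it through.** **Tracing a patient's arm through the text.**

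1. Randomisation fixes the volunteer's arm, not the patient's.
2. Data collection and follow-up has a volunteer offered. No sequence, list or chance rule is stated for which one.
3. The Discussion allows another volunteer to be offered if needs are unmet. The criterion is response to the need, and arm is not mentioned.
4. The blinded external researcher covers who is selected and how they are followed up. Steps 2 and 3 concern which volunteer a selected participant receives, so the safeguard does not reach them.
5. Questionnaires are repeated monthly while the patient is under palliative care or until death, so a change of volunteer can fall between measurements.

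Following the text as written can therefore produce a change of arm related to need.

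**The plan's own figures first** (Participants): mean difference 3 on the HAD score, power 80%, confidence 95%, ICC 0.05, mean cluster size 7, loss 20%.

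- Design effect = 1 + (7 − 1) × 0.05 = 1.30, as stated.
- 20 volunteers × 7 = 140, as stated.
- The total of 140 cannot be derived from the stated inputs alone, because no SD is given. Back-solving: 140 × 0.8 / 1.3 / 2 = 43.08 effective per arm, and SD = 3 × √(43.08/2) / (1.96 + 0.84) ≈ 4.97.
- With an assumed SD of 5: 44 per arm, 88 × 1.3 = 114.4, and 114.4 / 0.8 = 143, close to 140.

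**Dilution, as an illustration.** Let a share s of one arm receive the other arm's care, with everyone analysed in the arm first assigned. Switchers are treated as having the other arm's full effect, so late switching would dilute less.

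- SE implied by the stated power = 3 / (1.96 + 0.84) = 1.071.
- Diluted effect = 3 × (1 − s). Power ≈ Φ(effect / SE − 1.96).
- s = 10%: effect 2.7; 2.7 / 1.071 − 1.96 = 0.56; power about 71%.
- s = 20%: effect 2.4; 2.4 / 1.071 − 1.96 = 0.28; power about 61%.

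**Sensitivity to the missing SD** (140 enrolled, 20% loss, design effect 1.3):

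- SD 4.5: 87% with no switching, 80% at s = 10%.
- SD 5: 80% with no switching, 71% at s = 10%.
- SD 6: 64% with no switching, 55% at s = 10%.

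Much of the spread from 80% to 55% comes from the SD. At any one SD, 10% switching costs roughly 8 to 9 percentage points.

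If both arms switched, the effect would be 3 × (1 − 2s). At SD 5, s = 10% gives 2.4 and about 61%; s = 20% gives 1.8 and about 39%.

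None of these figures includes bias from need-related sorting, which has no bound in the article and could run either way.

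**The case against.** The strongest reply is that the text says less than a worried reader may infer. Four stronger readings are tempting, and the article supports none of them.

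- **Inpatient volunteers pick their patients.** Settings says "volunteers come every afternoon to the rooms where they wish to offer accompaniment to patients and their relatives". The sentence describes the unit's routine, not a trial rule, and "they" could refer to the patients. The home-care sentence that follows makes the wish the patient's.
- **Patients are matched to volunteers by need from the outset.** The two statements about need are one contingency stated twice, and the Discussion makes it conditional. On the first link the article is silent.
- **Care teams steer patients who want technology to tech-volunteers.** The teams offer the service. No text says that they choose the individual or are told the allocations, although device use could reveal them.
- **One-year volunteer terms force changes of arm.** The article gives no duration of palliative care, so how often a patient outlasts a volunteer is unknown, and a successor could be of the same arm.

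It is also fair to say that the article does not state that replacements will come from the other arm, that intention to treat is named, and that a full protocol or analysis plan may hold a linking rule. The switching shares have no anchor in the text.

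All of that limits the point without removing it. The article does more than stay silent: its stated answer to what it calls the main risk is to offer volunteers by need, with no arm limit. A linking rule elsewhere would have to be reconciled with that sentence.

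**Conclusion.** The point holds in a limited form. A participant's arm is not fixed by any stated arm-independent rule, and it may change during follow-up through replacement by need. The article does not show that it will change, or how often.

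The power losses are illustrations. They rest on assumed one-arm switching of 10% or 20%, full crossover of effect, and either a standard error back-solved from the stated 80% power or an assumed SD. They show what crossover would cost, not what this plan will produce. Analysing by first-linked volunteer confines the harm from replacement to dilution. Analysing by the volunteer actually received would add bias that a larger sample does not remove. I rate this a cheap improvement: the gap is real and closing it takes little.

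**What to change.** For study participants only:

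1. Amend the sentence on unmet needs in the Discussion, and its counterpart in the strengths and limitations list, so that any replacement volunteer comes from the same arm. A list that groups volunteers by code lets this be done without showing the arm labels to the person arranging it.
2. Complete consent and baseline before a volunteer is named, and make the first link by availability in that setting (home or inpatient), not by need.
3. State that every participant is analysed under the arm and cluster of the first-linked volunteer, whatever happens later.
4. Log every volunteer who visits each participant, so that any crossover can be reported.

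The cost is less freedom to hand-match volunteers within the study, plus one log and a few sentences. A strict arm-blind queue would be harder to run with about 20 volunteers over two settings, and is not needed for these changes. People who want a volunteer but decline the study are unaffected. If recruitment has already closed, the analysis rule and a retrospective record of links can still be put in place.
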